#### **7.2.3. Follow-Up of Abnormal Laboratory Test Values**

In the event of clinically significant abnormal laboratory test values, the tests should be repeated immediately and followed up until they have returned to the normal range or an adequate explanation of the abnormality is found.

#### **7.2.4. Pregnancy**

If a subject becomes pregnant during the study, she will be taken off treatment and will be followed through the end of her pregnancy. The outcome of a pregnancy (for a subject or for the partner of a subject) and the medical condition of any resultant offspring must be reported to GSK (or designee). Forms for reporting pregnancies will be provided to the study sites upon request.

### **8. STATISTICAL METHODS, ANALYSES, AND DETERMINATION OF SAMPLE SIZE**

#### **8.1. Statistical and Analytical Plans**

Details of the planned analyses will be documented in a separate Statistical Analysis Plan.

**8.1.1. Analysis Populations**

The safety population will be defined as all subjects who received at least one dose of study drug.

The evaluable population will include subjects in the safety population who:

1. have a baseline and post-baseline tumor assessment, and
2. who have received at least 75% of protocol-mandated doses during the 8-week study treatment period;

as well as subjects who, prior to completing the 8-week Study Treatment Period:

1. require study drug discontinuation due to GSK1363089-related toxicity, or
2. have objective evidence of progressive disease.

All efficacy analyses will be performed on both the safety and the evaluable populations.

All safety analyses will be performed on the safety population.

All efficacy and safety analyses will be conducted on each cohort separately as well as together.

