### 3.4. Dose Reduction or Treatment Delay for Toxicity

For the purpose of this protocol and for assistance with making decisions regarding dose reduction or delays, the following CTCAE Grade 3 definitions have been slightly modified (modifications are in italics):

- Grade 3 hypertension *despite optimal antihypertensive therapy with one or more drugs* (see [Management of Treatment-Emergent Hypertension](#) for information regarding management of treatment-emergent hypertension)
- Grade 3 nausea, vomiting, or diarrhea *despite prophylaxis and/or treatment* (see Section [4.4.2](#) for information regarding supportive care treatment)

In the event of treatment emergent hepatotoxicity, irrespective of whether the investigator considers it related to study drug, the management guidelines described in Section [4.4.4](#) should be followed.

If a subject experiences a new onset of unacceptable symptoms or signs of toxicity (excluding hepatotoxicity which is covered above), but in the investigator's opinion should continue to receive study drug, study treatment may be delayed for up to 21 days, then resumed either at the same dose or at a reduced dose, according to the criteria set out in Sections [3.4.1](#) and [3.4.2](#). The details of how to dose-reduce subjects are set out in Sections [3.4.3](#) and [3.4.4](#).

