### **5.10.2. Replacements**

Subjects who do not receive any study drug will be replaced. If a subject is prematurely discontinued from the study for reasons other than GSK1363089-related safety and no outcome measures have been performed, he or she may be replaced.

If, after Amendment 4.0 is implemented, a subject consents to provide paired tumor biopsies, but subsequently is not able to provide the second of the paired biopsies, then that subject will be allowed to continue on study and will be eligible for inclusion in the safety and efficacy assessments. However, if by so doing, this would prevent at least 12 subjects being enrolled who do provide paired biopsies, then an extra subject will be enrolled.

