## 8.2. Determination of Sample Size

The trial will accrue 30 evaluable subjects in each Cohort, with or without confirmed c-MET amplification, as defined as  $\geq 3$  genomic copies of the *c-MET* gene. After the accrual of each cohort of 30 evaluable subjects, enrollment may be extended (to a maximum of 40 subjects) until at least eight subjects with confirmed c-MET amplification at 7q31, as defined as  $\geq 3$  genomic copies of the *c-MET* gene, are enrolled in each cohort. These will be stratified as follows:

- Stratum A: Subjects with confirmed *c-MET* amplification at 7q31.
- Stratum B: Subjects without confirmed *c-MET* amplification at 7q31

Additionally, as part of Amendment 4.0, there will be a requirement in Cohort 2 to have at least 4 evaluable subjects who meet a more stringent definition of *c-MET* gene amplification (i.e.  $\geq 2$  copies of *c-MET* per copy of chromosome 7; see Section 3.3.1 for a more detailed definition).

In the event that the enrolment of 30 evaluable subjects in Cohort 2 is completed before the target of 4 subjects with *c-MET* amplification, as defined by  $\geq 2$  copies of *c-MET* per copy of chromosome 7, has been reached, then extra subjects, with proven *c-MET* amplification, pre-screened by FISH, will be enrolled in the study, until the target is reached.

This sample size will allow an initial assessment of the tolerability of GSK1363089 in metastatic gastric cancer subjects, when dosed either in the intermittent 5&9 or daily schedules, building on the safety data from the two Phase I studies (77 subjects), which tested each of these schedules in subjects with a variety of solid tumors. Some hypothesis testing will also be possible with regards to the primary efficacy variable, which is the objective response rate (ORR), defined as the proportion of subjects for whom their best overall response is a confirmed CR or confirmed PR by RECIST:

For each Cohort, if at least 6 of the 30 evaluable subjects respond, this regimen of GSK1363089 will have demonstrated a response rate of 20%. This design is used to test the following hypothesis on the ORR:

Ho:  $P_o \leq 0.10$  versus  $P_a \geq 0.25$

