Assuming a type I error rate (alpha) of 0.10 and a type II error rate (beta) of 0.20, with 30 evaluable subjects and at least 6 observed responses ( $\geq 0.20$ ) subjects, there is a 0.0732 chance of falsely concluding this regimen is preliminarily effective if the true response rate is 0.10. And the chance for falsely rejecting the effect of the regimen is 0.2026 if the true response rate is 0.25. If additional enrollment is required and at least 8 of the 40 ( $\geq 0.20$ ) evaluable subjects respond, then the above two probabilities would be 0.0419 and 0.18196, respectively.

With the design of this study, the following table (Table 7) summarizes the expected lower bounds for the 1-sided confidence interval corresponding to the 6/30 or 8/40 scenarios respectively, for each cohort.

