**Note:**

- Subjects with a global deterioration of health status requiring discontinuation of treatment without objective evidence of disease progression at that time should be classified as having "symptomatic deterioration". Every effort should be made to document the objective progression even after discontinuation of treatment.
- In some circumstances, it may be difficult to distinguish residual disease from normal tissue. When the evaluation of complete response depends on this determination, it is recommended that the residual lesion be investigated (fine needle aspirate/biopsy) to confirm the complete response status.

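### The 6/30 response rule is tested on an evaluable set that omits some early failures, so its stated type I error does not carry over to all treated subjects

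*Combined protocol and SAP*

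**What the plan says.** Section 8.2 sets the rule for each cohort: "if at least 6 of the 30 evaluable subjects respond", the regimen is taken to have shown a 20% response rate. The hypotheses are a rate of at most 0.10 against at least 0.25. The design statement reads "Assuming a type I error rate (alpha) of 0.10 and a type II error rate (beta) of 0.20", and the attained figures are a "0.0732 chance of falsely concluding this regimen is preliminarily effective if the true response rate is 0.10" and a "chance for falsely rejecting the effect of the regimen is 0.2026 if the true response rate is 0.25". If enrolment is extended, the rule becomes 8 of 40, with 0.0419 and 0.18196. All four figures refer to evaluable subjects. The Synopsis (Number of Subjects) and section 3.3.1 continue enrolment until 30 subjects are evaluable.

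Section 8.1.1 defines the evaluable set. A subject needs a baseline and a post-baseline tumour assessment and must be one of those "who have received at least 75% of protocol-mandated doses during the 8-week study treatment period". Two early exits are also counted: discontinuation for drug-related toxicity, and objective progression, in each case before the 8 weeks are complete.

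Three other places bear on this:

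- Appendix F (note to Table 8) treats "global deterioration of health status requiring discontinuation of treatment without objective evidence of disease progression at that time" as a class of its own, symptomatic deterioration.
- Section 5.10.2 says of a subject who leaves early for "reasons other than GSK1363089-related safety and no outcome measures have been performed, he or she may be replaced".
- Section 3.4 states that, for toxicity, "study treatment may be delayed for up to 21 days".

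Sections 8.1.1 and 8.1.2 and the Synopsis also require the response rate, with an exact 95% confidence interval, in the safety population (everyone who took a dose).

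**The concern.** Whether a subject counts towards the rule is decided by facts observed after treatment begins. The first scheduled on-treatment scan is at week 8 (section 3.1.2), and a response must be confirmed at least 28 days after it is first seen (section 5.9.3.2). A subject who dies, deteriorates or withdraws before that scan can therefore hardly be a confirmed responder. If no objective progression was documented and the stop was not for drug toxicity, section 8.1.1 does not count that subject, and enrolment goes on until someone else fills the place.

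Removing near-certain non-responders can only raise the response rate. The primary objective (section 2) is the rate in subjects with the disease, and section 8.2 uses the rule to call the regimen preliminarily effective. At stake is how often a regimen with a 10% response rate in everyone treated would meet that description.

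The dose condition raises a separate question. It can remove subjects who were scanned and who followed the protocol but used a permitted delay.

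**Working it through.** **Inputs.** From section 8.2: n = 30 and r = 6 (or n = 40 and r = 8), p0 = 0.10, p1 = 0.25, alpha 0.10, beta 0.20. From section 3.4: a delay of up to 21 days. From the schedules: 56 daily doses in 8 weeks in Cohort 2, and 4 cycles × 5 = 20 doses in Cohort 1. The non-evaluable fraction f is not in the documents. It is assumed here to lie between 0% and 30%.

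**Step 1: the plan's own figures.** With X binomial(n, p), type I error is P(X ≥ r | p0) and type II error is P(X < r | p1).

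- 6/30: 0.0732 and 0.2026.
- 8/40: 0.0419 and 0.1820.

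These agree with section 8.2. The arithmetic is right for a response rate defined among evaluable subjects.

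**Step 2: a 10% rate in all treated subjects.** If a fraction f is non-evaluable and none of them would respond, the rate among evaluable subjects is 0.10/(1 − f), and the chance of passing is P(X ≥ r | n, 0.10/(1 − f)).

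| f | Evaluable rate | Passing 6/30 | Passing 8/40 |
|---|---|---|---|
| 0% | 10.0% | 0.073 | 0.042 |
| 5% | 10.5% | 0.089 | 0.054 |
| 10% | 11.1% | 0.109 | 0.070 |
| 20% | 12.5% | 0.164 | 0.119 |
| 30% | 14.3% | 0.251 | 0.204 |

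**Step 3: break-even with 0.10.** For 6/30 the tail equals 0.10 at p = 0.1086, so f = 1 − 0.10/0.1086 = 7.9%. Three non-evaluable among 33 treated is 3/33 = 9.1%, already above it. For 8/40 the tail equals 0.10 at p = 0.1201, so f = 16.7%.

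**Step 4: if some excluded subjects are responders.** Let g be the fraction of responders who are excluded. The evaluable rate is then 0.10(1 − g)/(1 − f). With f = 20% and g = 10% it is 0.1125, and the chance of passing 6/30 is 0.114. With g = f there is no inflation and the figure stays at 0.0732.

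**Step 5: the observed rate.** Six responders are 6/30 = 20.0% of evaluable subjects, but 6/33 = 18.2% of 33 treated or 6/38 = 15.8% of 38 treated.

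**Step 6: the dose condition.** In Cohort 2 a 21-day delay leaves (56 − 21)/56 = 35/56 = 62.5% of doses, below 75%. The limit is 14 missed doses (42/56 = 75%). In Cohort 1 one missed cycle leaves 15/20 = 75%, which still qualifies, and two leave 10/20 = 50%. Section 8.1.1 does not say whether doses withheld under a permitted delay count as mandated.

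**Step 7: the rule on all treated subjects.** Take the smallest r with P(X ≥ r | N, 0.10) ≤ 0.10.

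| N treated | r | Type I error | Power at 25% |
|---|---|---|---|
| 30 | 6 | 0.073 | 0.797 |
| 32 | 6 | 0.094 | 0.847 |
| 33 | 7 | 0.042 | 0.753 |
| 34 | 7 | 0.048 | 0.782 |
| 35 | 7 | 0.055 | 0.808 |
| 38 | 7 | 0.080 | 0.872 |

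**The case against.** The strongest reply is that the all-treated response rate with its exact interval is already required, so any dilution would appear beside the evaluable figure. That is true and limits the harm. But no section names that estimate as primary or gives it a cutoff. If the two populations disagree, only the evaluable one has a rule.

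Several further points stand:

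- The main failure routes, objective progression and drug-toxicity discontinuation, remain in the denominator. Extra imaging is allowed when clinically indicated, and Appendix F asks sites to try to document progression after a clinical stop. Both shrink f, but neither covers death without a scan, an unrelated event or withdrawal.
- Replacement under section 5.10.2 is optional and limited to subjects without outcome measures. Enrolling until 30 are evaluable has the same effect without it.
- Section 8.2 offers the test modestly, and no study action depends on it: Cohort 2 opens once Cohort 1 has enrolled, whatever the responses.
- Section 8.1 defers detail to a separate analysis plan that is not in the supplied text and may name a primary population. That would not by itself change section 8.2.

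Two stronger readings are tempting. A reader might infer that alpha of 0.10 is not held. The documents do not support this: the attained figure is 0.0732, the breach needs f above 7.9% (16.7% for 8/40), and no f is given. A reader might also infer that dropping dose-delayed subjects inflates the response rate. Those subjects may include responders, so the direction is unknown.

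**Conclusion.** The point holds in a conditional form. The evaluable denominator biases the response rate behind the 6/30 (8/40) rule upward relative to all treated subjects, through early death without documented progression, symptomatic deterioration, unrelated stops and withdrawal. The direction of that part is clear. Its size depends on f. For 6/30 the chance of passing at an all-treated rate of 10% moves from 0.073 to 0.109 at f = 10% and 0.251 at f = 30%, if every excluded subject is a non-responder. It is smaller if responders are excluded too.

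A non-evaluable fraction above 7.9% is plausible in advanced disease, where section 1.1 puts median survival below 10 months and section 4.2 admits ECOG status up to 2, but this is a judgement and not a figure in the plan. The stated error rates are not miscalculated. They answer a question about evaluable subjects only. The 75%-of-doses condition is a gap in definition with a bias of unknown sign.

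**What to change.** In section 8.2, name the safety (all-treated) population as primary for the response rate and for the rule. Count anyone without a confirmed complete or partial response as a non-responder. For each cohort, use the smallest cutoff with exact one-sided alpha ≤ 0.10 at p0 = 0.10 for the number actually treated (for example 7 responders at N = 35 or N = 38), and keep the evaluable analysis as supportive.

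The change is mainly wording and uses a population already defined, but it is not free. The reported rate may be less favourable. Power at 25% dips below 0.80 at some N (0.753 at 33, 0.782 at 34), so power should be restated for the actual N. If 25% was meant as the rate among evaluable subjects, the loss is larger: with 30 evaluable of 33 treated the all-treated rate is 0.25 × 30/33 = 22.7%, and power with r = 7 is about 0.65. Holding 0.80 could then need more subjects or a restated alternative.

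A minimum alternative stays within section 8.1.1. Count death, symptomatic deterioration and any other discontinuation before the week-8 scan as evaluable non-responders, and keep subjects who have a post-baseline scan whatever fraction of doses they took.

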**8.1.2. Primary Efficacy Analysis**

The primary efficacy variable is the objective response rate (ORR), defined as the proportion of subjects for whom their best overall response is a confirmed CR or confirmed PR by RECIST.

ORR will be summarized using the point estimate of the proportion and an exact 95% confidence interval, for each cohort separately.

If the observed response rate is high enough to warrant an investigation of variables associated with response, exploratory stratified and logistic regression analyses may be performed. Variables that may be considered include age, sex, disease characteristics, performance status, and previous treatment history.

**8.1.3. Secondary Efficacy Analyses**

Secondary efficacy variables are:

- 1) Disease stabilization rate (DSR) is defined as the proportion of subjects for whom the best overall response is confirmed PR, confirmed CR, or SD
- 2) Duration of progression-free survival (PFS) is defined as the time between the date of first dose of study drug and death or disease progression.
- 3) Duration of Stable Disease is defined as the time between the date of first dose and death or disease progression, in subjects whose best overall response was not PD.
- 5) Duration of overall survival is defined as time between date of death and date of first dose.

DSR will be summarized using the point estimate of the proportion and an exact 95% confidence interval.

PFS, OS, and duration of stable disease will be summarized using Kaplan-Meier methods. Kaplan-Meier plots and data listings will also be presented.

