#### Evaluation of Target Lesions

**Complete Response (CR)** – disappearance of all target lesions.

**Partial Response (PR)** – at least a 30% decrease in the sum of the LD of target lesions, taking as a reference, the baseline sum LD.

**Stable Disease (SD)** – neither sufficient shrinkage to qualify for PR nor sufficient increase to qualify for progressive disease (PD), taking as a reference, the smallest sum LD since the treatment started.

**Progressive Disease** – at least a 20% increase in the sum of the LD of target lesions, taking as a reference, the smallest sum LD recorded since the treatment started or the appearance of one or more new lesions.

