**Confirmation Criteria**

- To be assigned a status of PR or CR, a confirmatory disease assessment should be performed no less than 28 days after the criteria for response are first met.
- To be assigned a status of SD, follow-up measurements must have met the SD criteria at least once after study entry at a minimum interval of 6 weeks.

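### Duration of stable disease is computed for every best response other than PD, so it pools responders with SD and leaves unscanned subjects unsettled

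*Combined protocol and SAP*

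**What the plan says.** Section 8.1.3 gives three definitions that bear on this point:

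- Duration of stable disease: "Duration of Stable Disease is defined as the time between the date of first dose and death or disease progression", taken "in subjects whose best overall response was not PD".
- PFS: "Duration of progression-free survival (PFS) is defined as the time between the date of first dose of study drug and death or disease progression", with no restriction by response.
- DSR: "the proportion of subjects for whom the best overall response is confirmed PR, confirmed CR, or SD".

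Appendix F treats CR, PR and SD as separate categories. SD means too little shrinkage for PR and too little growth for PD. It also has to be measured: "To be assigned a status of SD, follow-up measurements must have met the SD criteria at least once after study entry". The shortest interval allowed is 6 weeks. Section 5.9.3.2 repeats that rule. Table 8 lists only CR, PR, SD and PD as overall responses.

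Section 8.1.1 adds: "All efficacy analyses will be performed on both the safety and the evaluable populations". The safety population needs one dose and no scan. The evaluable population admits subjects who stop early for drug-related toxicity, again without requiring a scan. Section 3.1.2 places the on-treatment tumor assessment at 8 weeks.

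**The concern.** Duration of stable disease and PFS share the same start and the same end. The analysis set is therefore the only thing that gives this endpoint a meaning of its own, and the set is not the one the name promises.

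Two groups other than SD can enter. Confirmed responders enter on any reading. Dosed subjects with no post-baseline scan enter if the wording is taken literally, since they have no PD on record. Their time to death would then count as time in stable disease, although Appendix F could never have assigned them SD.

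The endpoint is a named secondary objective in Section 2, reported for each cohort and for both together. Comparing the two regimens is an exploratory objective. If the mix of responders and early failures differs between cohorts, the two medians could differ, or agree, for reasons unrelated to how long stable disease lasts.

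**Working it through.** **The plan's own figure.** The protocol states no figure for this endpoint, so there is none to reproduce. Its only error rates belong to the response-rate rule in Section 8.2. They reproduce by exact binomial: 0.0732 and 0.2026 for at least 6 of 30, and 0.0419 and 0.1820 for at least 8 of 40. Nothing here depends on them.

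**Step 1: who is in which set.**

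| Subject | SD under Appendix F | DSR numerator | Best response other than PD |
|---|---|---|---|
| Best response SD | yes | yes | yes |
| Confirmed CR or PR | no | yes | yes |
| Dosed, no post-baseline scan | no | no | not settled; yes if read literally |
| Best response PD | no | no | no |

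The second row follows from the text without inference. The third row does not. Unscanned subjects are in the safety population, and those who stopped for drug-related toxicity are in the evaluable population too. Nothing in Sections 8.1.1 to 8.1.3 or Appendix F takes them out of this analysis. Subjects classed in Appendix F as having symptomatic deterioration, if never scanned, are in the same position.

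**Step 2: direction.** Responders tend to progress later than subjects with SD. Unscanned subjects who die before week 8 have the shortest times. The two groups pull the median in opposite directions.

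**Step 3: illustration.** Every input is an assumption except the 6-week SD minimum, the week-8 scan and the 28-day confirmation interval. Time t is in weeks from first dose, with no censoring.

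- SD: 35% of dosed subjects, median 16, no event before week 6. S(t) = 2^(−(t−6)/10) for t > 6.
- Responders: 10%, median 32, no event before week 12 (week 8 plus 28 days). S(t) = 2^(−(t−12)/20) for t > 12.
- Unscanned early failures: 15%, events uniform over weeks 0 to 8. S(t) = 1 − t/8, and 0 after week 8.

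The pooled median solves Σ w·S(t) / Σ w = 0.5.

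- SD only: 16.0 weeks.
- SD plus responders, at t = 18.65: (35 × 0.416 + 10 × 0.794)/45 = 22.5/45 = 0.50. Median 18.7 weeks.
- All three groups, at t = 13.67: (35 × 0.5875 + 10 × 0.9437 + 15 × 0)/60 = 30.0/60 = 0.50. Median 13.7 weeks.

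**Step 4: range.** Keep SD at 35% and vary the other two groups.

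- No responders, 15% unscanned, at t = 10.85: 35 × 0.714/50 = 0.50. Median 10.9 weeks.
- 20% responders, none unscanned, at t = 20.65: (35 × 0.362 + 20 × 0.741)/55 = 0.50. Median 20.7 weeks.
- 20% responders, 15% unscanned, at t = 15.95: (35 × 0.502 + 20 × 0.872)/70 = 0.50. Median 16.0 weeks; the two effects cancel.

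Plain exponentials with the same SD and responder medians, and a median of 4 weeks for the unscanned group, give 12.3 weeks for all three groups and 18.4 without the unscanned. They fit the protocol poorly. They place 1 − 2^(−6/16) = 23% of SD subjects at an event before week 6, which Appendix F rules out, and leave 2^(−8/4) = 25% of the unscanned group event-free past the week-8 scan.

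**The case against.** **Unscanned subjects may have no best response at all.** Appendix F takes the overall response as the best one recorded, and Table 8 allows only CR, PR, SD and PD. A subject with no scan has nothing recorded, so an ordinary reader could take any response other than PD to mean CR, PR or SD. This stands. A reader might infer that unscanned early deaths are definitely counted as stable disease; the documents do not support that. They show only that handling is unstated, so two analysts could report different medians from the same data.

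**The endpoint may be the companion to DSR.** DSR itself counts CR and PR, so the sponsor may have meant how long disease was controlled. This also stands, and it makes renaming as good a remedy as restricting to SD. It does not rescue the present wording: the label still says stable disease, and the set is not written as the DSR numerator.

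**Details may be in the separate analysis plan.** Section 8.1 announces one. Handling of unassessed subjects could be settled there, but no different definition appears in the documents supplied.

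**Little depends on it.** The endpoint is a Kaplan-Meier summary with no test, power or decision attached. PFS, DSR and data listings are reported as well, and the cohorts are not randomized. This is correct and limits the weight of the point.

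**Conclusion.** The point holds in a limited form. Confirmed responders are pooled into an endpoint named for stable disease; that is certain from Section 8.1.3 read with Appendix F. Whether unscanned subjects are pooled too is not settled by the text. If they are, the set matches neither SD nor the DSR numerator.

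The size cannot be fixed from the documents. Under the assumptions shown, the reported median could lie anywhere from about 10.9 to 20.7 weeks against 16 for SD alone, or show no net shift. A reader might infer from one such figure that the endpoint is biased downward by a known number of weeks. That would need both the disputed reading and an assumed mix, and with responders alone the shift is upward. Nor do the documents show that the comparison between cohorts is actually distorted; they show only that it could be if the mix differs. The response-rate rule, PFS and DSR are untouched. It should be corrected because the mismatch is in the stated rule and is cheap to remove.

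**What to change.** Choose one of two definitions in Section 8.1.3 and carry it into the analysis plan:

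1. Keep the name and restrict the set to subjects whose best overall response is SD under Appendix F, including the 6-week minimum.
2. Rename the endpoint duration of disease stabilization and restrict it to confirmed CR, confirmed PR or SD, the same subjects as the DSR numerator.

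In both cases state that subjects with no post-baseline tumor assessment are not in the set, including those with symptomatic deterioration who were never scanned. They remain in PFS and overall survival.

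The cost is one line of text. Option 1 leaves fewer subjects in the analysis. Neither option changes the sample size, the error rates or the primary analysis.
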